Few studies have investigated the effect of RT among older women with varying comorbidity burden, and to our knowledge, none of the previous studies have evaluated long-term HRQOL trajectories post RT within older women treated in the modern era. Thus, the proposed study aims to examine the effects of RT on long-term HRQOL trajectories and survival outcomes among older women with low-risk breast cancer in an observational setting. Minimizing the potential bias due to treatment selection and controlling for potential differences in confounding factors between treatment groups are essential in observational comparative effectiveness studies without randomized treatment [30]. To mitigate this concern, first, we will only select older women with low-risk breast cancer whose main treatment plan includes BCS and endocrine therapy with RT being an option. Among this group of women, only 3.3% undergo chemotherapy [1]; thus, the confounding effect of chemotherapy on HRQOL and survival outcomes is minimal. Second, to further balance out the potential confounding factors between the 2 groups, we will use inverse probability of treatment weighting (IPTW) methods, a type of propensity score analysis [31-34], which we have applied successfully in other projects [35,36]. All potential confounding variables will be included in the statistical models when deriving the weights for each group.

This comparative effectiveness study will utilize a national sample of older women to provide much-needed evidence regarding the combined effects of RT and comorbidity on HRQOL (subjective outcome) and survival (objective outcome) in older women. This research has 2 aims.

Regarding Aim 1, we will examine the effect of RT on the HRQOL trajectory over time and its interaction with comorbidity burden in older women with low-risk breast cancer (n=465) using IPTW-adjusted growth mixture models. We hypothesize that the HRQOL trajectory will differ by treatment status and comorbidity burden, and the largest decline will be observed in older women with the highest comorbidity burden.

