#### Measurements

The primary exposure variable will be adjuvant RT. We will consider BCS alone and BCS with adjuvant RT as the treatments. The SEER data provide information on radiation treatment and the sequence of surgery and radiation.

The outcomes of Aim 1 will be HRQOL scores measured over a 5-10 years of follow-up (ie, prediagnosis through post-treatment). MHOS measures HRQOL using the Medical Outcomes Study 36-item Short Form (SF-36) through the year 2005 and the Veterans RAND 12-item Health Survey (VR-12) from the year 2006 onwards. These 2 questionnaires have been validated in many languages and are widely used in HRQOL research, including that involving breast cancer patients [38]. The NCI developed algorithms to convert SF-36 scales to VR-12 scales; hence, the latter will be used across all cohorts in the current study. The VR-12 items correspond to 8 health domains, namely physical functioning, role limitations due to physical problems, role limitations due to emotional problems, bodily pain, social functioning, mental health, vitality, and perceptions of general health. These 12 items are then summarized into 2 summary scores: the physical component summary score and the mental component summary score. These 2 summary scores are standardized scores (mean 50, SD 10), which are normed based on the general US population. A total of 465 women who met the eligibility criteria for Aim 1 completed MHOS multiple times (an average of 3 times). We will sort the data according to the prediagnosis (T_0_) and postdiagnosis (T_1_…T_10_) timelines, specifying the time lapse from the cancer diagnosis. The prediagnosis HRQOL (T_0_, n=465) will be assessed using the survey conducted within 24 months prior to the diagnosis date recorded in SEER. The postdiagnosis HRQOL (T_1_…T_10_) will be assessed using the survey completed after the diagnosis of breast cancer. We collected 465 data points for the precancer diagnosis, 508 data points within 2 years postdiagnosis, 166 data points for 2-<5 years postdiagnosis, and 92 data points for ≥5 years postdiagnosis. The number of patients who completed MHOS in each time frame is presented in Table 1.

**Table 1 table1:** Number of patients who completed MHOS in each time frame (N=465).

Survey time to cancer diagnosis (months), t	Prediagnosis and postdiagnosis HRQOL timelines	n (%)
–24<t<0	T_0_	465 (100)
0≤*t*<12	T_1_	253 (54)
12≤*t*<24	T_2_	255 (55)
24≤*t*<36	T_3_	79 (17)
36≤*t*<48	T_4_	50 (11)
48≤*t*<60	T_5_	37 (8)

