60≤*t*<72	T_6_	29 (6)
72≤*t*<84	T_7_	21 (5)
84≤*t*<96	T_8_	17 (4)
96≤*t*<108	T_9_	8 (2)
108≤t	T_10_	17 (4)

We considered comorbidity burden as the effect modifier. Prediagnosis comorbidity is an important component of this study, as it likely impacts HRQOL and survival outcomes adversely while also affecting treatment decisions. The presence and number of comorbidities as well as their severity are important. However, the severity of each comorbidity is not available from MHOS, whereas the functional limitations and symptoms related to these comorbidities are. To account for functional limitations and symptoms as a component of comorbidity, we created a new variable named “comorbidity burden class” with 24 self-reported items (ie, 12 chronic medical conditions, 7 functional difficulties, and 5 symptoms) in MHOS (Textbox 1) using latent class analysis. This technique has been applied successfully to identify healthy patients or comorbidity profiles of cancer patients in studies using SEER-MHOS and the National Cancer Database [39,40] when the severity of comorbid conditions is not available. To identify the prediagnosis comorbidity burden class, the survey completed within 24 months before cancer diagnosis was evaluated. Latent class analysis is a subset of structural equation modeling, which is used to categorize subjects into a set of homogeneous groups (eg, k distinct membership classes of comorbidity) according to the observed variables (eg, self-reported chronic medical conditions, functional status, and symptoms). We anticipated that this procedure would suggest 3-5 distinct categories. We selected the most parsimonious number of classes using the Bayesian information criterion to find the best fitting numbers of classes. The classes of comorbidity burden will be tested as effect modifiers.

Items included in latent class analysis modeling for comorbidity burden class.

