#### Statistical Analysis Plan

Regarding the descriptive analyses, the baseline characteristics of the study population will be described in terms of the mean and SD for continuous variables and frequencies with percentages for categorical variables. Descriptive analyses will be conducted to compare demographic, tumor-related, and treatment-related factors for the study population by their treatment status (BCS and RT vs BCS only). Differences in continuous variables and categorical variables will be assessed by *t* tests and chi-square tests, respectively. All analyses will be conducted using SAS 9.4 (SAS Institute Inc.) and R 4.0.1 (R Core Team), and a 2-tailed α level of .05 will denote statistical significance.

The probability of the treatment received by a particular person will be estimated by generalized boosted models using receipt of RT as the dependent variable and the baseline characteristics, such as age at diagnosis, race/ethnicity, smoking status, income, education, SEER region, rurality, disease stage, tumor grade, tumor subtype, and year of diagnosis, as the independent variables. Then, the inverse of the probability of receiving the treatment the patient actually received conditional on the observed covariates will be calculated and included as a weight for each patient in subsequent analyses [41]. Balances in potential confounding factors between the treatment groups will be assessed using diagnostic tools, including chi-square tests for categorical variables, *t* tests for continuous variables, and the standardized mean differences between 2 groups [42]. The standardized mean difference will be calculated as the difference in means or proportions divided by a pooled estimate of SD. A standardized mean difference≥10% will be considered as evidence of imbalance [43].

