We will also test for the existence of a differential effect of RT on the HRQOL trajectory according to the comorbidity burden class by incorporating interaction terms in the model. If we lack the power to detect statistically significant differences according to comorbidity level but point estimates for the effect of RT indicate that meaningful differences are present across levels of comorbidity, separate estimates will be reported for each comorbidity class. As each participant completed MHOS at different time points, growth mixture modeling is more flexible and sensitive than traditional repeated-measures analysis [44]. It can also capture nonlinear patterns [44].

Regarding the sensitivity/subgroup analysis, if the sample size allows, subgroup analysis by age and tumor stage will be conducted to examine whether the findings are generalizable to all patients satisfying the eligibility criteria.

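### After a non-significant RT-by-comorbidity interaction, Aim 1 makes class-specific RT effects reportable on the condition that their point estimates look different, with no threshold stated

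*Protocol article*

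**What the plan says.** All of this is in the protocol article. The Introduction makes modification by comorbidity part of Aim 1: trajectories are expected to differ by treatment and comorbidity burden, and "the largest decline will be observed in older women with the highest comorbidity burden". Under Aim 1, Measurements, burden is a latent class variable: "We anticipated that this procedure would suggest 3-5 distinct categories".

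The Aim 1 Statistical Analysis Plan tests a differential RT effect by class "by incorporating interaction terms in the model", and for all analyses "a 2-tailed α level of .05 will denote statistical significance". It then adds a rule for the case where the test does not reach significance. The rule opens "If we lack the power to detect statistically significant differences according to comorbidity level" and continues that if "point estimates for the effect of RT indicate that meaningful differences are present across levels of comorbidity, separate estimates will be reported" for each class.

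The article does not define a meaningful difference, either on the summary-score scale or as points per year. It gives no criterion for telling lack of power from absence of interaction, and it does not commit to reporting the class estimates whatever they show.

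**The concern.** The rule looks at the class-specific estimates and then decides whether to report them. Estimates selected because they differ will, on average, overstate how much they differ. Attributing the non-significant test to lack of power presupposes that a real difference exists, although the same result is expected when there is none.

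The rule is likely to be used. The article gives no power calculation (465 is a count of eligible women), and under plausible assumptions the interaction test has low power, so the non-significant branch is the probable one. The Discussion intends the joint effects of RT and comorbidity to inform shared treatment decisions. Class-specific differences that reach print by this route could be read as a basis for treating women in different classes differently.

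**Working it through.** The plan has no figure of its own to reproduce. The check asks how often the rule is met when the RT effect is the same in every class.

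**Inputs from the article:** 465 women; 3 to 5 classes; two-sided alpha 0.05; summary scores with SD 10 (general-population norm).

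**Assumptions, because the article does not give them:** equal class sizes; 60% of women receiving RT; design effect (deff) from weighting of 1.0 to 1.3; one mean difference per woman; thresholds of 3 and 5 points. SD 10 also applies to a change score if the within-woman correlation is 0.5, since 10 × √(2 × 0.5) = 10. A correlation of 0.7 gives 10 × √(2 × 0.3) = 7.75.

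**Step 1. Standard error of the RT effect in one class.** With k classes and n = 465/k,

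SE = SD × √[deff × (1/(0.6n) + 1/(0.4n))].

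For k = 3, n = 155, SD 10 and deff 1.0: 10 × √(1/93 + 1/62) = 1.64 points. With deff 1.3 it is 1.87. For k = 4 the range is 1.89-2.16, and for k = 5 it is 2.12-2.41.

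**Step 2. Simulate the rule.** Draw k independent normal estimates with a common mean and this SE (400,000 replicates). Test heterogeneity with Cochran's Q on k − 1 degrees of freedom at 0.05. Count a replicate when Q is not significant and the largest minus the smallest estimate exceeds the threshold.

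| Classes | SD 10, > 3 points | SD 10, > 5 points | SD 7.75, > 3 points | SD 7.75, > 5 points |
|---|---|---|---|---|
| 3 | 0.35-0.44 | 0.03-0.09 | 0.17-0.26 | near 0 |
| 4 | 0.63-0.71 | 0.19-0.31 | 0.42-0.53 | 0.03-0.10 |
| 5 | 0.80-0.86 | 0.40-0.54 | 0.65-0.74 | 0.15-0.27 |

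Each range runs from deff 1.0 to deff 1.3. Requiring a non-significant test matters: at SD 10, counting every replicate would add about 0.05 to each entry (for example 0.40-0.49 instead of 0.35-0.44).

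**Step 3. How likely is the non-significant branch?** Take two classes whose true RT effects differ by a given amount, with SD 10, 65% receiving RT (assumed), no weight inflation and 93 to 155 women per class (465/5 to 465/3). The SE of the contrast is 10 × √[2 × (1/(0.65n) + 1/(0.35n))], which is 3.07 at n = 93 and 2.38 at n = 155. Two-sided power is 16-24% for a 3-point difference and 37-56% for a 5-point difference. A non-significant test is thus the likely outcome, or close to an even chance, even when a difference of this size is real.

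**The case against.** The strongest reply is that showing stratum estimates is good practice, and that the rule promises estimates, not a declaration. This stands in part. A reader might infer that the plan will claim effect modification after a non-significant test, and so inflate false claims. The text does not say so: it keeps alpha at 0.05 and, in describing the model, ties interpretation to significant coefficients. The probabilities above are chances that the reporting condition is met, not chances of a false claim.

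A reader might also infer that similar-looking class estimates will be withheld. The text is silent on that case. It makes no commitment to show them and none to suppress them.

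The scale is also open to challenge. The plan's RT effect on trajectory is a yearly slope from a growth model with about three surveys per woman. The check uses one mean difference per woman, so a 3-point range here is not 3 points per year. The thresholds are assumed, and with three classes and a 5-point threshold the condition is rarely met by chance. These points limit the magnitude, not the form of the rule.

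The missing definition of meaningful could stand in a fuller analysis plan. But the conditional rule is stated in the article itself, and a threshold would make it less elastic without ending its dependence on the results.

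In the plan's favour, comorbidity class is a single modifier named in advance, and the classes were formed before the outcome analyses began. This is not an open search for subgroups. Nor should the point be carried over to Aim 2: comorbidity is a modifier there too, but that section contains no such conditional rule.

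**Conclusion.** The point holds as one about result-dependent reporting on a headline question of Aim 1. After a non-significant interaction, attributed to lack of power, class-specific RT effects become reportable on condition that they look different by an unstated amount.

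With no true interaction, noise meets that condition often unless the threshold is large and the classes few. At SD 10 the probability ranges from 0.35 to 0.86 for a 3-point threshold and from 0.03 to 0.54 for a 5-point threshold, across 3 to 5 classes. At SD 7.75 with three classes it falls to 0.17-0.26 and near 0. These figures rest on equal classes, a 60/40 RT split, design effect 1.0-1.3 and a mean-difference scale, so they illustrate the problem and do not predict this study's rate. That the rule depends on the results follows from the text alone and needs none of these assumptions.

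The documents do not establish that homogeneous results will be hidden or that modification will be declared without a significant test. The change is worth making before the outcome analysis, and it is small.

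**What to change.** Replace the conditional sentence in the Aim 1 Statistical Analysis Plan with a commitment along these lines: the RT effect in each comorbidity class will be reported with its 95% CI, together with the interaction test or contrast and its CI, whatever the result. If the interaction is not significant, the class estimates will be labelled exploratory, and the text will state that modification was not shown and give the range of differences compatible with the data.

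This removes the selection entirely, because reporting no longer depends on the estimates, and it keeps the class-specific information that the present sentence aims to provide. Naming one contrast in advance, such as highest minus lowest burden class, is an option and not a requirement. The cost is one rewritten sentence and one table that is always shown.

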### Aim 2: Examine the Effect of RT on Breast Cancer-Specific Mortality

#### Study Design and Study Population

A retrospective cohort study design will be used in the context of Aim 2. Older women who were enrolled in Medicare and completed the MHOS will be selected for this study. The inclusion criteria were (1) a diagnosis of primary breast cancer between 1998 and 2010 (to ensure at least 5 years of follow-up after a cancer diagnosis) and report to SEER, (2) a diagnosis of low-risk breast cancer, (3) ≥65 years of age at diagnosis given the Medicare framework, (4) receipt of BCS (lumpectomy, segmental resection, quadrantectomy, or partial mastectomy) as primary treatment for breast cancer, and (5) completion of at least 1 MHOS within 24 months prior to breast cancer diagnosis (to allow the evaluation of the prediagnosis comorbidity burden). Participants will be excluded from the study if (1) they had a previous cancer diagnosis (other than nonmelanoma skin cancer), (2) they had more than 1 primary tumor at diagnosis, (3) they received treatment outside of standard time frames (ie, treatment initiated 1 year after cancer diagnosis), (4) they received RT before surgery, or (5) their vital status was missing.

#### Measurements

The exposure variables are the same as those of Aim 1, namely BCS alone and BCS with adjuvant RT. We will consider vital status and cause of death as the outcomes. The main outcome for Aim 2 will be mortality (all-cause mortality and breast cancer-specific mortality considering nonbreast cancer mortality as a competing event). The SEER data file provides the vital status of participants and the date and causes of death, which have been verified through the National Death Index. Survival will be calculated from the date of diagnosis to the last known follow-up date or December 31, 2016, whichever comes first. As in the case of Aim 1, the comorbidity burden will serve as the effect modifier. The confounding factors will match those of Aim 1.

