#### Statistical Analysis Plan

The descriptive analyses outlined for Aim 1 will apply to Aim 2 as well. Regarding the IPTW, we will apply the same procedures as in Aim 1 to the dataset to obtain a weight for each woman. The effect of RT on mortality will be assessed via 5-year survival curves of the study population using the Kaplan-Meier method, which will incorporate the IPTW. To estimate the effect of RT and comorbidity on mortality, we will use the weighted Cox proportional hazards model to obtain the IPTW-adjusted relative hazard of 5-year overall and cause-specific mortality from the date of diagnosis. IPTW-adjusted subdistribution hazard ratios with 95% CIs will be reported. The proportional hazards assumption will be assessed using the Schoenfeld residuals test, which measures the correlation between residuals of each covariate and time and evaluates the interactions with time in the survival models. Sensitivity analysis will be performed to examine whether the censoring may be informative rather than noninformative. We will consider 2 extreme possibilities: events occurred immediately after censoring or later than any other observed events.

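### Aim 2 starts the survival clock at diagnosis but groups women by RT received later, after surgery, which builds in immortal time bias favouring RT

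*Protocol article*

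**What the plan says.** Protocol article, Methods, Aim 2, Measurements: "Survival will be calculated from the date of diagnosis to the last known follow-up date or December 31, 2016, whichever comes first". The Aim 2 Statistical Analysis Plan repeats the start point. The weighted Cox model is to give the "IPTW-adjusted relative hazard of 5-year overall and cause-specific mortality from the date of diagnosis", and weighted Kaplan-Meier curves cover the same 5 years.

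On exposure, Aim 2 Measurements says: "The exposure variables are the same as those of Aim 1, namely BCS alone and BCS with adjuvant RT". Aim 1 Measurements gives the source: "The SEER data provide information on radiation treatment and the sequence of surgery and radiation". The groups therefore reflect treatment recorded as received.

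Aim 2, Study Design and Study Population, requires BCS in both groups, excludes RT given before surgery, and excludes treatment outside standard time frames ("ie, treatment initiated 1 year after cancer diagnosis").

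The weights come from the Aim 1 procedure: the inverse probability of the treatment actually received, given baseline covariates. The only sensitivity analysis stated for Aim 2 concerns informative censoring. Neither the Aim 2 text nor the Limitations section mentions a landmark, delayed entry or RT as a time-dependent exposure.

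**The concern.** Follow-up starts at diagnosis, but a woman enters the RT group only through something that happens afterwards and that she must be alive to receive. If she dies after BCS while waiting for RT, her death is charged to BCS alone. If she reaches RT, the whole waiting time is added to the RT group as event-free follow-up.

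No baseline covariate records survival to RT, so balance on those covariates, however good, leaves the problem in place. The informative-censoring analysis does not touch it either, because these women are misclassified, not censored.

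The direction matters. The Introduction hypothesizes that RT improves 5-year mortality, and it also cites a randomized trial with no significant survival benefit from adding RT. A distortion towards RT could be read as support for the hypothesis, and the Discussion intends the results to inform shared treatment decisions.

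**Working it through.** The article gives no event count, target hazard ratio or power for Aim 2, so there is no figure of its own to reproduce. The check asks what the stated analysis returns when RT has no effect.

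**Inputs from the article:** clock from diagnosis; 5-year horizon; BCS required in both groups; RT only after surgery; treatment begun a year after diagnosis excluded; n = 634; two-sided 0.05. RT use in such women is said to exceed 50%, but that is a cited figure and not this cohort's share.

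**Assumptions:** all-cause hazard 0.04 per year; BCS survived at month 1; intended RT share p = 0.5 or 0.7; RT start uniform over months 2-3, 2-6 or 2-12. The last range is the outer bound implied by the one-year exclusion.

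**Formula.** Among women alive at surgery, let D be the probability of death by year 5 and m the probability that a woman intended for RT dies before it starts. With no RT effect, deaths per woman in the cohort are p(D − m) in the RT group and (1 − p)D + pm in BCS alone. The misfiled women die early and carry little person-time, so person-time stays close to p : (1 − p). Hence

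HR ≈ (D − m) / (D + m·p/(1 − p)).

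**Constant hazard.** D = 1 − exp(−0.04 × 59/12) = 0.1785. Mean delay after surgery is 1.5, 3 or 6 months, so m ≈ 0.0050, 0.0099 or 0.0198.

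| RT start | p = 0.5 | p = 0.7 |
|---|---|---|
| Months 2-3 | 0.1735/0.1835 = 0.95 | 0.1735/0.1902 = 0.91 |
| Months 2-6 | 0.1686/0.1884 = 0.89 | 0.1686/0.2016 = 0.84 |
| Months 2-12 | 0.1587/0.1983 = 0.80 | 0.1587/0.2247 = 0.71 |

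**First-year hazard halved.** D = 1 − exp(−0.02 × 11/12 − 0.04 × 4) = 0.1633; m ≈ 0.0025, 0.0050 or 0.0099.

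| RT start | p = 0.5 | p = 0.7 |
|---|---|---|
| Months 2-3 | 0.1608/0.1658 = 0.97 | 0.1608/0.1691 = 0.95 |
| Months 2-6 | 0.1583/0.1683 = 0.94 | 0.1583/0.1750 = 0.90 |
| Months 2-12 | 0.1534/0.1732 = 0.89 | 0.1534/0.1864 = 0.82 |

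Cox models fitted to simulated cohorts under the same assumptions agree with every cell to within 0.01.

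**In deaths.** At n = 634, p = 0.7 and months 2-12, the misfiled deaths number 634 × 0.7 × 0.0198 ≈ 9, out of 634 × 0.1785 ≈ 113 in all. At p = 0.5 and months 2-3 they number 634 × 0.5 × 0.0050 ≈ 2.

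**False positives favouring RT** (simulated, n about 634, nominal 2.5%; p = 0.5 to p = 0.7): about 5-7%, 9-15% and 20-42% for the three delay ranges. With first-year hazard halved they are about 3-4%, 5-8% and 9-16%.

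**After the fix.** In simulations under no effect, a 12-month landmark gave HRs of 0.99-1.01, as did RT entered as a time-dependent exposure.

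**The case against.** The best reply concerns size. BCS is an entry criterion, so deaths before surgery are excluded from the cohort and do not fall to BCS alone. The article gives neither the distribution of RT start times nor early mortality. Women with T1-2N0 disease who were fit for surgery and had answered a survey in the preceding 24 months may well die less often in the first year. With short delays and halved early hazard, the HR is 0.95-0.97 and the false-positive rate is close to nominal. All of this stands and is built into the figures above.

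A reader might infer three stronger things that the article does not support:
- That RT starts are spread over a full year. The exclusion speaks of treatment in general, not RT, and says nothing about how starts are distributed. Months 2-12 is an outer bound.
- That the bias would by itself produce the hypothesized survival benefit. That is plausible only with long delays and undiminished early mortality.
- That the same sizes apply to breast cancer-specific mortality. The figures are for all-cause mortality. The cause-specific bias depends on how many breast cancer deaths occur between surgery and RT, and it is not quantified here.

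One might also point to lag time since treatment, listed among the potential confounders under Aim 1. It is not in the list of propensity-model covariates, and adjusting for it would not realign the start of follow-up.

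That a journal article is condensed is no answer here, because the start date, the fixed groups and the model are all stated.

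**Conclusion.** The concern holds. As written, Aim 2 sets time zero before exposure is determined, and nothing stated corrects for it. The direction was towards RT in every all-cause scenario examined. The size is uncertain: small with short delays and low early mortality, large (an HR of about 0.71-0.80 under no effect) with long delays and constant hazard. These ranges rest on the assumed 4% yearly hazard, surgery at month 1, an RT share of 50-70% and uniform RT starts. The mechanism needs none of these, only some deaths between surgery and planned RT. It should be corrected before the survival analysis is run.

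**What to change.** Start the clock for both groups at a landmark at the end of the plan's own treatment window, 12 months after diagnosis. Include women alive then, fix RT status at that date, and estimate the weights in that set. Run the Kaplan-Meier, Cox and competing-risk analyses from there.

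State the horizon: for example, to 5 years after diagnosis, or 5 years after the landmark. The second is feasible, since a woman diagnosed at the end of 2010 has 6 years to December 31, 2016, which leaves 5 after the landmark.

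RT start dates are not needed if the one-year exclusion can be applied to RT. The article describes only receipt and sequence, so this should be confirmed. If dates exist, RT as a time-dependent exposure is an alternative that keeps early deaths.

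The cost is a change of analysis wording and of estimand, which becomes mortality among women alive at 12 months. First-year deaths leave the comparison: 634 × (1 − exp(−0.04)) ≈ 25 women at the assumed hazard, about half that if first-year hazard is halved.
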